### Randomisation

Patients will be allocated in a 1:1 ratio to the treatment group and standard care group (receiving early inotropes vs. standard fluid management). A permuted block randomisation method with variable block sizes of two, four and six and stratified by site will be used to allocate eligible patients to a study group. Randomisation will be performed by the site investigator, research coordinator or treating clinician by opening the next sequential sealed opaque envelope which are prepared using a randomisation sequence prepared by The University of Queensland, Brisbane, Australia.

### Blinding

No blinding will be performed; the intervention will be open labelled. The main aim of this pilot study is to ascertain the feasibility of the study protocol. Blinding of fluid vs. inotropes would be logistically almost impossible to achieve. In addition, given the study is enrolling acutely ill children on a trajectory of potential rapid deterioration, clinicians need to be able to access the amount of delivered interventions for safety reasons.

### Study Interventions

Allocated treatment will be started as soon as possible after randomisation. The allocated intervention arm will be administered if the clinician is continuing to treat for signs of septic shock. The trial compares ***early inotropes*** started after 20 mL/kg fluid resuscitation with ***standard care*** (Figure 2).

**Figure 2 F2:**
[figure not shown]
Treatment algorithm for RESPOND ED. Children with sepsis having received an initial fluid bolus are randomized **(A)** to *early inotropes*, defined as initiation of adrenaline infusion after 20 ml/kg fluid bolus **(B)**, vs. *standard care*, defined as provision of 40–60 ml/kg fluid boluses before inotropes are started **(C)**. ED SMO, Emergency Department Senior Medical Officer.

#### Early Inotropes

Patients in the intervention arm will receive an infusion of intravenous adrenaline immediately after randomisation, i. e. after the initial fluid bolus of 20 mL/kg (1,000 mL fluid bolus in patients >50 kg). Adrenaline will be initiated at 0.05 to 0.1 (up to 0.3) microgram/kg/min as per institutional guidelines. For the administration, adrenaline 1 mg will be diluted in 49 mls of 5% Dextrose. The dilution is used to hasten drug delivery and response to drug rate changes, to reduce risks with extravasation, and to facilitate peripheral application. Drug delivery will occur through dose error reduction software for infusion devices to ensure safe delivery of applied standardised drug concentrations. In emergency situations, adrenaline can be given through a peripheral intravenous, intraosseous, or central venous access line. Once started, adrenaline should be delivered for 60 min at a dose titrated to age-based physiological targets in patients who show signs of stability before weaning the drug. Patients who are successfully weaned off adrenaline within <4 h can in principle be admitted to the ward, yet should be reviewed by PICU staff within 4–6 h after transfer from ED. In patients deteriorating despite adrenaline infusion, the dose rate should be increased and admission to PICU with appropriate monitoring sought as per local practice.

#### Standard Care

In the standard arm, patients will receive standard care as per site specific protocols based on international guidelines (11, 13). Specifically, patients in the standard arm will receive 40–60 mL/kg of fluid bolus therapy prior to initiating inotropes, thus, 20–40 mL/kg bolus fluid *after* randomisation (in addition to the 20 mL/kg bolus fluid, or 1,000 mL fluid bolus in patients >50 kg, which has to be administered to meet enrolment criteria). Further fluid and inotrope decisions in the standard care arm are at the discretion of the treating physician. The standard care is aligned with education provided at the study sites through the Paediatric Sepsis Pathway project (Queensland Sepsis collaborative) since 2018, which advocates for the administration of sepsis resuscitation bundles as per the Surviving Sepsis Campaign.

Patients who improve in <4 h can in principle be admitted to the ward as per local practice. In patients deteriorating despite 40–60 ml/kg fluid boluses, inotropes should be commenced, and the dose rate should be increased until stabilisation occurs. Admission to PICU with appropriate monitoring should be sought as per local practice.

#### Other General Medical Care and Decisions on PICU Admission

Treating clinicians can escalate therapy as clinically indicated. Specifically, they can decide to change adrenaline dose rates, administer further fluid boluses, and consider additional inotropes or vasoactive agents to manage septic shock refractory to initial treatment. Fluid boluses in both arms can be balanced or unbalanced crystalloid (Compound Sodium Lactate, sodium chloride 0.9%, PlasmaLyte 148) or colloid (4% albumin) as per clinician preference. Other care including respiratory management, antibiotics, glucose and electrolyte control, transfusion, sedation, and extracorporeal life support should be provided at the discretion of the treating physician according to local practice. Decisions for admission to PICU must be based on medical and nursing assessment according to local practice.

### Study Outcomes

This pilot study includes feasibility outcomes, as well as clinical primary and secondary outcome measures, and proxy measures of intervention efficacy (Table 2). The *feasibility outcomes* include consent rates; compliance measures such as time to inotropes, amount of fluid delivered during the first 24 h; and protocol violations. The *clinical primary outcome* is survival free of organ dysfunction, censored at 28 days. Organ dysfunction will be assessed by pediatric Sequential Organ Failure Assessment (pSOFA) scores (23). Patients dying within 28 days of presentation will be considered as zero days to correct for the competing effect of mortality on duration of organ dysfunction. Patients discharged alive from PICU to the ward or home not requiring ongoing respiratory or renal support, and not under palliative care will be assumed to have no organ dysfunction after PICU discharge. *Secondary clinical outcomes* include PICU free survival, survival free of inotrope support and free of multi-organ dysfunction (defined as >1 organ with a pSOFA score >0), mortality, and PICU and hospital length of stay. In addition, we will obtain Pediatric Overall Performance Category and Functional Status Score at 28 days (24). Long-term follow-up will be performed at 6 months post randomisation using assessment of quality of life using neurodevelopment, quality of life and functional status, and will be reported separately. *Proxy measures of intervention efficacy* include the proportion of study participants with a blood lactate level <2 mmol/L at 6, 12 and 24 h, time to reversal of tachycardia [defined by the upper age-specific thresholds for Systemic Inflammatory Response Syndrome (22)], and time to reversal of shock (defined as cessation of inotropes for at least 4 h). Ancillary studies assessing sepsis-related costs are pre-planned but will be reported separately.

**Table 2 T2:** Outcomes assessed.

**Outcome**	**Criterium**	**Definition**
Feasibility of the protocol	Compliance with study protocol	• Recruitment rates; proportion of eligible randomised, proportion of eligible consented using prospective consent and consent to continue. • Time to initiation of inotropes between the control and the early inotrope arm • Amount of fluid delivered (in mLs per kg) during the first 24 h between the control and the early inotrope arm • Protocol violations
Primary clinical outcome	Survival free of organ dysfunction	• Organ dysfunction defined as pediatric Sequential Organ Failure Assessment (pSOFA) score >0. Patients dying within 28 days of presentation will be allocated zero days to correct for the competing effect of mortality on duration of organ dysfunction. Patients discharged alive from PICU to the ward or home not requiring ongoing support, and not being palliative, will be assumed to have no organ dysfunction after PICU discharge.
Secondary	Patient centered outcomes	• Survival free of inotrope support at 7 days • Survival free of multiorgan dysfunction at 7 days
		• 28-day mortality • Survival free of PICU censored at 28 days • PICU length of stay • Hospital length of stay • Functional Status Score and modified Pediatric Overall Performance Category at 28 days • Neurodevelopment, Quality of life and Functional status 6 months post enrolment
	Proxy measures of intervention efficacy	• Amount of fluid (mLs per kg) received during the first h, and by 4, 12, and 24 h post enrolment • Proportion with lactate <2 mmol/l at 6, 12, and 24 h post enrolment • Time to reversal of tachycardia during the first 24 h^*^. • Time to shock reversal, defined as cessation of inotropes for at least 4 h censored at 28 days

* *Goldstein et al. (22)*.

We consider a separation of ≥10 ml/kg fluid bolus administration during the first 24 h, and a difference in inotrope commencement time of ≥20 min between the two arms as an indication of feasibility of the protocol leading to a measurable and potentially clinically relevant difference in the treatment delivered.

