### Statistical Analysis Plan

#### Sample Size

A recruitment period of 24 months is the projected time to achieve the required sample size of 40 participants. The size of the pilot (*N* = 40) was chosen to reflect about 10% of a full trial to yield sufficient data in relation to feasibility. We estimate that ~50 children each year are treated for septic shock in the main participating ED. Assuming that 30–40% of children will meet exclusion criteria, and anticipating 50% enrolment rates, completion within 24 months is projected to be feasible.

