#### Analysis

Using the Consolidated Standards of Reporting Trials (CONSORT) flow chart (Figure 1) (20), we will describe the number of screened patients, those meeting inclusion and exclusion criteria, the number consented, and numbers of those who withdrew consent. In addition, we will provide in the text details of the consent process, including proportion of children with prospective consent vs. consent to continue, reasons why consent to continue was used, and time from enrolment to obtaining written consent in hours (IQR). Time from randomisation to initiation of allocated treatment will be reported. Descriptive statistics will be utilised to report on demographics, clinical history and baseline clinical characteristics of patient allocated to each of the study arms (Supplementary Table 1). Statistical comparison between the characteristics of the two arms at baseline will not be undertaken. The feasibility and clinical outcome measures (Supplementary Tables 2, 3) will be compared with the estimate of the difference and corresponding 95% confidence intervals (CIs). Continuous outcomes are assumed to be non-normally distributed, and as such quantile regression will be used to generate the CIs. A test of two proportions will be used for the binary outcomes. Analyses will be by intention-to-treat. Adverse events will be presented descriptively (Supplementary Table 4).

We will graphically compare physiological measures, heart rate, systolic blood pressure, pulse pressure (systolic minus diastolic blood pressure), shock index (heart rate divided by systolic blood pressure) and use of fluid bolus volume (in ml/kg) over time, using values measured during the first 24 h, comparing the intervention group to the control group, using values measured during the first 24 h.

We anticipate that <30% of RESPOND ED study patients will be co-enrolled into a concomitant study investigating metabolic resuscitation, named RESPOND PICU (ACTRN12619000829112) (27). Given that the study is a pilot feasibility study, analyses on RESPOND ED will occur separately from RESPOND PICU.

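### Lactate at 6, 12 and 24 h is compared, in the shown text, only as the proportion below 2 mmol/L; adding a full-scale comparison would cost little and give a more precise estimate

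*Protocol article*

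**What the plan says.** The Study Outcomes section and Table 2 define the lactate outcome as "Proportion with lactate <2 mmol/l at 6, 12, and 24 h post enrolment", one of four proxy measures of intervention efficacy.

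The Analysis section fixes the method by type of variable. For dichotomies: "A test of two proportions will be used for the binary outcomes". For continuous variables: "Continuous outcomes are assumed to be non-normally distributed, and as such quantile regression will be used to generate the CIs". Outcomes are to be reported as estimated differences with 95% confidence intervals. The measures to be compared graphically over the first 24 h are heart rate, systolic pressure, pulse pressure, shock index and fluid bolus volume. Lactate is not among them.

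On size, the Sample Size section says "A recruitment period of 24 months is the projected time to achieve the required sample size of 40 participants" and that this number "was chosen to reflect about 10% of a full trial to yield sufficient data in relation to feasibility". The Randomisation section adds "Patients will be allocated in a 1:1 ratio to the treatment group and standard care group", so about 20 children per arm. No power, effect size, lactate distribution or expected control proportion is stated.

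**The concern.** Lactate is a continuous measurement. Once it is cut at 2 mmol/L, a child who falls from 8 to 2.5 mmol/L scores the same as a child who does not change, while 1.9 and 2.1 mmol/L count as a full difference. With about 20 children per arm, that loss of information matters to the width of the interval.

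The Discussion says the pilot is to inform the design of a full trial powered for benefit. For that purpose a planner wants an estimate of the between-arm difference and a measure of spread. A difference in proportions is imprecise at this size, and it supplies neither a lactate SD nor a between-arm ratio.

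**Working it through.** **Inputs from the article.** N = 40 (Sample Size), 1:1 allocation (Randomisation), hence n = 20 per arm. The cut is at 2 mmol/L (Table 2). The test is of two proportions (Analysis). A two-sided 5% level is inferred from the 95% intervals. There is no stated power to reproduce.

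**Assumptions, none given in the article.** Log lactate is normal with equal SD in both arms. The standardised difference d favours the early-inotrope arm. The control proportion below 2 mmol/L is pc. All 20 children per arm are analysed.

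**Formulas.**
- Proportion below 2 mmol/L in the other arm: pt = Φ(Φ⁻¹(pc) + d).
- Power with the cut: exact binomial enumeration of the pooled z test, 20 per arm.
- Power on log lactate: noncentral t with 38 degrees of freedom and noncentrality d·√(n/2) = d·√10.

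**One cell in full.** For d = 0.8 and pc = 50%, pt = Φ(0 + 0.8) = 79%. The pooled z test has power 49%. The noncentrality is 0.8 × 3.162 = 2.53, which gives t-test power 69%. The loss is about 20 points.

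**Main range.**

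| d | pc → pt | Power with cut | Power, t-test on log lactate | Loss (points) |
|---|---|---|---|---|
| 0.5 | 30% → 49% | 23% | 34% | 11 |
| 0.5 | 50% → 69% | 23% | 34% | 11 |
| 0.5 | 70% → 85% | 20% | 34% | 14 |
| 0.8 | 30% → 61% | 48% | 69% | 21 |
| 0.8 | 50% → 79% | 49% | 69% | 20 |
| 0.8 | 70% → 91% | 39% | 69% | 31 |
| 1.0 | 30% → 68% | 67% | 87% | 20 |
| 1.0 | 50% → 84% | 67% | 87% | 20 |
| 1.0 | 70% → 94% | 52% | 87% | 35 |

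**Wider range.** At d = 0.3 the loss is about 4 to 6 points. At d = 1.0 with pc = 80%, power is 37% against 87%, a loss of about 50 points. For d from 0.3 to 1.0 and pc from 20% to 80%, the cut has less power in every cell examined; only the size changes.

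**Rank test.** In a simulation of 4,000 trials per cell over the main range, the gain over the cut was 11 to 36 points with the t-test and 9 to 34 with the Mann-Whitney test. The rank test therefore recovers nearly all of the loss without requiring normality.

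**The plan's own continuous method.** Near the null, the efficiency of a cut relative to a comparison of means is φ(z)²/[p(1 − p)]. At p = 50% this is 0.159/0.25 = 64%; at p = 30% or 70% it is 0.121/0.21 = 58%. A comparison of medians has efficiency 2/π = 64%, no better than a cut at the median. Accordingly, the asymptotic gain from median regression over the proportion test is only about 1 to 7 points for pc of 20% to 50%, and 5 to 22 points at 70%. In a 1,500-replicate simulation median regression did worse than the proportion test: 13–15% against 21–23% (d = 0.5), 40–41% against 47–51% (d = 0.8), and 58–60% against 66–68% (d = 1.0).

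**Interval width.** The plan reports intervals, so the same point can be put that way. With both arms at 50%, the half-width for the difference is 1.96 × √(2 × 0.25/20) = 31 points; with both at 30%, it is 1.96 × √(2 × 0.21/20) = 28 points.

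**The case against.** The strongest reply is that power is the wrong yardstick. The trial was sized for feasibility, the article promises estimates with intervals, and power for benefit is left to a later trial. The only numerical feasibility criteria, given after Table 2, are a fluid separation of at least 10 ml/kg and an inotrope timing difference of at least 20 min. Lactate enters neither. This stands and sets the priority. It does not remove the point, because the same loss appears as a wider interval in the estimate handed to the full trial.

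Second, a normalisation threshold is easy to interpret, and the article does not contradict itself by using one. That also stands, and is why the proportion should be kept.

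Third, treating lactate as continuous under the stated plan would lead to quantile regression, which gains little and may do worse. This is correct. The improvement needs the full scale and a more efficient method together.

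Three stronger readings are tempting and are not supported:
- A reader might take a loss of 11 to 35 points as a property of this trial. It is not: the effect size, control proportion, distribution and comparator are all assumed.
- A reader might infer that lactate is never analysed on its full scale. Supplementary Tables 2 and 3, to which the Analysis section refers, are not shown, so this can be said only of the shown text.
- A reader might suppose that lactate is one of very few efficacy signals. Table 2 also lists fluid volumes, time to reversal of tachycardia, time to shock reversal and several clinical outcomes.

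**Conclusion.** The point holds as a low-priority improvement and does not show an error in the plan. In the shown text, lactate is compared only after a cut at 2 mmol/L, which discards information relative to a log-scale or rank-based comparison of the same values. Under the assumptions set out above, the cost is about 11 to 35 points of power in the main range and about 4 to 50 points in the wider one. The direction is consistent across both ranges; the size cannot be fixed from the article. What would be gained is precision in one of several proxy measures, for use in designing the full trial. No conclusion about feasibility depends on it.

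**What to change.** Keep the proportion below 2 mmol/L in Table 2. For each of 6, 12 and 24 h, add a full-scale comparison: the ratio of geometric means (back-transformed difference in mean log lactate) with 95% CI or, where log-normality is doubtful, a rank-based comparison. State in the Analysis section that lactate is an exception to the default quantile regression.

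The cost is about one line in Table 2 and one in the Analysis section, one more estimate per time point, and one departure from the default continuous method. No new data are needed, because the numeric value is already required to classify each child.

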### Participants

#### Inclusion and Exclusion Criteria

Included will be children aged between 28 days and 18 years, where the treating clinician decides to treat for septic shock and administer intravenous antibiotics and an intravenous fluid bolus. Randomisation will occur after participants have received at least 20mL/kg fluid bolus in the last 4 h (or 1,000 mL fluid bolus in patients weighing over 50 kg), and the treating clinician must have decided to continue treating due to ongoing signs of shock. The exclusion criteria relate to patient characteristics which interfere with the study intervention and presence of chronic conditions which can interfere with the clinical outcome, as detailed in Table 1.

**Table 1 T1:** Inclusion and exclusion criteria.

**Rule**	**Criterium**	**Definition**
Inclusion	Age	• Aged ≥28 days and <18 years
	Illness	• Treated for sepsis
	Treatment	• Received at least 20 ml/kg fluid bolus in the last 4 h and clinician decides to continue treating signs of shock
	Consent	• Parental/caregiver consent prior to or after enrolment
Exclusion	Age	• Preterm babies born <34 weeks gestation that have a corrected age of <28 days
	Treatment	• Received ≥40 mL/kg of fluid boluses during the 4 h pre-enrolment • Inotrope infusion commenced pre-enrolment • Lack of access (intraosseous, central venous or peripheral) to administer fluids and/or inotropes after 60 min of enrolment
	Co-morbidities	• Cardiomyopathy or chronic cardiac failure • Chronic hypertension due to cardiovascular or renal disease, requiring regular antihypertensive treatment. • Known chronic renal failure (defined as requiring renal replacement therapy) • Known chronic hepatic failure • Palliative care patient/patient with limitation of treatment (not for inotropes, cardiopulmonary resuscitation, extracorporeal membrane oxygenation, intubation or ventilation)
	Illness severity	• Cardiopulmonary arrest in the past 2 h requiring cardiopulmonary resuscitation of >2 min duration, or death is deemed to be imminent or inevitable during this admission. • Major bleeding with haemorrhagic shock • Sepsis is not likely to be the cause of shock
	Previous study enrolment	• Enrolment in RESPOND study <6 months prior

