#### Screening and Consenting

Participants will predominantly be screened and recruited in the ED but can be recruited in PICU (Figure 1). Consent will be obtained from the guardians with the additional option to consent for biobanking. Where possible, prospective consent will be sought. Due to the emergency nature of septic shock, it is anticipated that in certain situations timely informed consent may not be feasible. In this circumstance a consent-to-continue approach will be applied [i.e., patients can be enrolled in the study if prospective consent cannot be obtained in a timely manner, but data can only be used in the analysis if the parents thereafter provide their written consent to continue in the study; also termed “deferred” or “delayed” consent (21)]. Informed consent will be sought from the parent/guardian by the study team or medical officer as soon as practical.

Screening will start at the time when the medical team decides to treat a patient for sepsis as per the institutional sepsis pathway (Queensland Paediatric Statewide Sepsis Pathway, which is being used at all study sites) to enable a pragmatic screening entry point. The trial does not mandate specific physiological thresholds to assess shock, rather the point of enrolment reflects the decision by the treating clinician to start a sepsis treatment bundle. Clinicians are advised to give a first fluid bolus of 20 mL/kg (or 1,000 mL fluid bolus in patients >50 kg) as per SSC guidelines irrespective of any decisions regarding enrolment in the study. Clinicians can give this amount of fluid as one bolus or split into aliquots of smaller amounts of bolus fluid.

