Physiological parameters and study treatment (fluids and inotropes) will be collected upon randomisation, then at 20-min intervals during the first 4 h, and at six, 12 and 24 h subsequently. The total fluid given will be captured at one, four, 12 and 24 h. Organ dysfunction and organ support will be collected upon randomisation, by 24 h and thereafter daily whilst treated in PICU for a maximum of 28 days. In addition, we will capture initiation of antibiotic therapy, intravenous steroids, duration of inotrope and/or vasopressors and respiratory support, PICU discharge, hospital discharge, death and cause of death. Protocol deviations and reasons for such will be recorded.

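### Time to reversal of tachycardia is a censored, coarsely read time, but the only method offered for it is quantile regression, so its medians can hide or exaggerate a difference

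*Protocol article*

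**What the plan says.** All references are to the protocol article.

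- **Outcome.** Table 2 (Study Outcomes) lists "Time to reversal of tachycardia during the first 24 h" among the proxy measures of intervention efficacy. Tachycardia itself is defined, "defined by the upper age-specific thresholds for Systemic Inflammatory Response Syndrome". The next entry in the table has an explicit cut-off: "Time to shock reversal, defined as cessation of inotropes for at least 4 h censored at 28 days". The lactate proxy is a set of fixed-time proportions: "Proportion with lactate <2 mmol/l at 6, 12, and 24 h post enrolment".
- **Entry.** Table 1 relies on clinician judgement: "Received at least 20 ml/kg fluid bolus in the last 4 h and clinician decides to continue treating signs of shock". Screening and Consenting adds: "The trial does not mandate specific physiological thresholds to assess shock".
- **Readings.** Data Collection schedules physiological parameters at randomisation, "then at 20-min intervals during the first 4 h, and at six, 12 and 24 h subsequently".
- **Analysis.** Continuous outcomes are taken as non-normal, and "quantile regression will be used to generate the CIs". Binary outcomes get a test of two proportions. Analyses are by intention-to-treat. No time-to-event method is named.

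**The concern.** Three features of this outcome do not suit quantile regression for a continuous variable.

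1. A child still tachycardic at 24 h, or who dies first, has no reversal time, only a lower bound.
2. After hour 4 the scheduled readings place a reversal only within a gap of 2, 6 or 12 hours. If the time is the first reading below threshold, later reversals can take only the values 6, 12 or 24 h.
3. A child who is not tachycardic at randomisation has nothing to reverse, yet intention-to-treat keeps that child in the comparison.

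Setting non-reversers to 24 h seems natural, but it gives them the same value as children who reversed between 12 and 24 h. The recorded median then moves in steps. Depending on where the true medians fall, a step can swallow a difference or enlarge it. The pilot is meant to inform a full trial, so a proxy whose result depends on coding and reading times is a weak guide.

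**Working it through.** **Inputs from the article.** Readings every 20 minutes to 4 h, then at 6, 12 and 24 h; window 24 h; 40 children allocated 1:1, so 20 per arm; 95% confidence intervals. The sample size is not based on power and no reversal rate is given, so there is no planned figure to reproduce.

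**Assumptions.** Reversal times are exponential, a reversal is dated at the first reading at or after it, and a range of true medians is tried.

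**Step 1: recorded medians with non-reversers set to 24 h.** For true median m, the proportion reversed by time t is 1 − 2^(−t/m). The recorded median is the first reading at which this reaches 50%; otherwise it is 24 h.

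| True median (h) | by 4 h | by 6 h | by 12 h | by 24 h | Recorded median (h) |
|---|---|---|---|---|---|
| 24.0 | 10.9% | 15.9% | 29.3% | 50.0% | 24 |
| 13.8 | 18.2% | 26.0% | 45.2% | 70.0% | 24 |
| 11.0 | 22.3% | 31.5% | 53.1% | 78.0% | 12 |
| 6.1 | 36.5% | 49.4% | 74.4% | 93.4% | 12 |
| 8.0 | 29.3% | 40.5% | 64.6% | 87.5% | 12 |
| 5.3 | 40.5% | 54.2% | 79.0% | 95.6% | 6 |
| 4.0 | 50.0% | 64.6% | 87.5% | 98.4% | 4 |
| 2.0 | 75.0% | 87.5% | 98.4% | 100.0% | 2 |

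Reading the rows in pairs:

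- 24.0 vs 13.8 h: a true gap of 10.2 h is recorded as 0.
- 11.0 vs 6.1 h: a true gap of 4.9 h is recorded as 0. The 6.1 h arm misses the 6 h step narrowly (49.4%), which shows how unstable the recorded median is.
- 8.0 vs 5.3 h: a true gap of 2.7 h is recorded as 6 h.
- 4.0 vs 2.0 h: recorded correctly.

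**Step 2: non-reversers left out.** Take 70% vs 50% reversed by 24 h. The rates are −ln(0.3)/24 = 0.0502 per hour and ln(2)/24 = 0.0289 per hour. Medians among reversers are −ln(0.65)/0.0502 = 8.6 h and −ln(0.75)/0.0289 = 10.0 h. Both lie between the 6 h and 12 h readings, so both are recorded as 12 h.

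**Step 3: children not tachycardic at entry.** Take true medians of 16.0 and 8.9 h. With non-reversers at 24 h these read 24 vs 12 h. If 20% of each arm are not tachycardic and are coded 0, they read 12 vs 12 h. This too is close to a step: in the faster arm 0.2 + 0.8 × 0.374 = 49.9% are at or below 6 h.

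**Step 4: is another method better on the same readings?** Trials of 20 per arm were simulated. The median difference (non-reversers at 24 h) counted as detected when its 95% bootstrap interval excluded 0; the log-rank test, censored at 24 h, when p < 0.05. Ranges span repeat runs.

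| True medians (h) | Median difference | Log-rank |
|---|---|---|
| 16 vs 6.4 | 24–25% | 67–68% |
| 8 vs 4.4 | 10–13% | 36–43% |
| 4 vs 2 | 26% | 49% |

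For 16 vs 6.4 h, the median difference on exactly known times capped at 24 h was detected in 52% of trials. So the coarse readings account for the fall from 52% to 24%. The rest is the difference between comparing one median and comparing whole curves. Exponential times favour the log-rank test, and a bootstrap interval on so few distinct values is conservative, so the size of the advantage is indicative only.

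**The case against.** **The article is condensed.** How to code non-reversers, deaths and children without baseline tachycardia for one proxy is detail that a full protocol, data dictionary or analysis plan commonly holds. That stands, and the missing coding rule is not the point. The point is that the method and reading times that are stated do not fit together, and Step 1 shows this under a sensible coding.

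**The link is inferred.** The Analysis section applies its methods to feasibility and clinical outcome measures, and the text of Study Outcomes names proxies as a separate class. Table 2, however, places them under secondary outcomes, and no other method is offered for a time. The reversal time might also be its own field taken from the bedside chart rather than from the scheduled readings. Both reservations stand. A chart-derived time would remove the coarse gaps but not the censoring.

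**A stronger reading is tempting:** that the comparison will be made only among children who reversed. The article does not say that non-reversers are dropped, and intention-to-treat points the other way. Nor is the outcome undefined, since threshold and window are both stated. With a 24 h cut-off, a median also tolerates right-censoring while more than half of each arm reverses.

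**Fixed-time proportions might seem a full substitute.** They are not. For medians of 4 vs 2 h, the proportion at 12 h detects the difference in only 14% of simulated trials, against 49% for the log-rank test. With 70% vs 50% and 20 per arm, the difference of 20 points has a Wald 95% interval of about −10 to +50 points (1.96 × √(0.21/20 + 0.25/20) = 0.30).

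**Little depends on it.** The feasibility criteria are fluid separation and inotrope timing, and heart rate over 24 h will be compared graphically. That stands and keeps the point minor.

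**Conclusion.** The concern holds as a mismatch between a stated method and the data it would receive. Quantile regression, the only method offered for a time such as this, accounts for neither the 24 h cut-off nor the 2, 6 and 12 h gaps in late readings, and some children may have nothing to reverse.

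The direction of the effect is not fixed. A reader might infer that the plan will hide a real benefit. It can (24.0 vs 13.8 h reads as no difference), but it can also exaggerate one (8.0 vs 5.3 h reads 12 vs 6 h), and it does almost nothing if most reversals come before 4 h. Which case applies depends on reversal rates that the article does not give; all those used here are assumed.

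In the scenarios simulated, a time-to-event analysis of the same readings detected the difference more often than the median comparison, including when reversal was early. The importance is low: one proxy in a 40-child feasibility pilot with no power claim.

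**What to change.** In the Analysis section, state for this outcome:

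- **Analysis set:** randomised children whose heart rate is above the age threshold at randomisation, with the number excluded shown by arm.
- **Method:** a time-to-event comparison on the recorded readings, either interval-censored or discrete-time/log-rank, in place of quantile regression.
- **Censoring and death:** censor at 24 h; count a child who dies before reversal as not reversed, kept at risk to 24 h.
- **Description:** report the proportion reversed at 4, 6, 12 and 24 h by arm beside the main comparison, not as a replacement for it.

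The scheduled readings and the age thresholds already support this, so no new data are needed. The cost is a little more analysis work and a smaller analysis set for this one proxy.
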